### Preoperative evaluation

A diagnosis of colon cancer must be pathologically confirmed before the surgery, using the biopsy specimen acquired from the colonoscopy. An enhanced CT scan of the abdominal and pelvic cavity is performed to localize the lesion. A CT colonography (virtual colonoscopy) or double-contrast barium enema can be performed when necessary.

An enhanced CT scan of the abdomen and pelvis can also provide information about the depth of tumor infiltration, the status of the regional lymph node metastasis, and the involvement of adjacent organs. A whole body enhanced CT scan can also demonstrate distant metastatic disease, such as liver, lung, and even peritoneum metastases. If necessary, other examinations including abdominopelvic MRI, contrast-enhanced ultrasound of the liver, endoscopic ultrasound, whole body bone scan, and positron emission tomography (PET)-CT can be used to facilitate the preoperative evaluation.

### Surgery

Surgical procedures for the two groups require sharp dissection strictly following the anatomical planes (also called embryonic planes) [2], including both the anterior and posterior aspects of the mesocolon, and separate the Toldt’s fascia from the retroperitoneum with an intact package of the tumor and its main lymphatic drainage (see Additional file 2). Complete mobilization of the mesocolon and complete removal of the vessels and lymph nodes inside will be achieved. The main differences between the two groups include the extent of lymphadenectomy (D2 versus D3); and whether or not to dissect the lymphoadipose tissues at the root of the mesocolon, which cover the anterior surface of the superior mesenteric artery (SMA) and vein (SMV), and the tissues surrounding the root of the middle colic artery.

There is no difference between the two groups in the extent of longitudinal resection. All procedures are basically a right hemicolectomy. The ileum is divided at 5–10 cm of the cecum. For cancer of the cecum and ascending colon, only the right branches of the middle colic vessels are divided centrally, and the colon is divided right at the level of the middle colic vessels. Cancer of the hepatic flexure and the right third of the transverse colon requires true central ligation of the middle colic artery and vein with resection of the transverse colon in the proximity of the splenic flexure, as well as a central tie of the right gastroepiploic artery and vein.

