Since Hohenberger first proposed the concept of complete mesocolic excision (CME) in 2009, the principle of CME has been gradually accepted and increasingly applied by colorectal surgeons as an optimal colectomy approach for colon cancer [2, 3]. According to this principle, the extent of lymphadenectomy of the radical right colectomy is similar to that of D3 lymph node dissection, which was advocated by the Japanese Society for Cancer of the Colon and Rectum (JSCCR) in the twentieth century [4]. In CME, the central vascular ligation (CVL) enables more radical removal of the metastatic lymph nodes. The resection in the mesocolic plane guarantees radical excision of the tumor and the potential vascular or neural infiltration in the whole regional draining area, which theoretically would improve the oncological outcome in comparison with the conventional right colectomy with D2 lymphadenectomy. However, compared to D2 dissection, laparoscopic CME or D3 dissection imposes a longer learning curve for the surgeons and a higher surgery-related risk for patients due to the complicated surgical anatomy involved in the laparoscopic approach, especially the dissection in the vicinity of the superior mesenteric vessels [5–8]. Neither the National Comprehensive Cancer Network (NCCN) guidelines nor the European Society for Medical Oncology (ESMO) guidelines have clearly defined the extent of lymphadenectomy of the radical right colectomy [9]. D3 lymphadenectomy was also advocated for locally advanced colorectal cancer by the Chinese standard for diagnosis and treatment of colorectal cancer, but CME was not mentioned [10]. In addition, all the results indicating improved survival rate of CME surgery compared to traditional D2 dissection were drawn from retrospective studies [2, 11–15]. Therefore, a well-designed prospective clinical trial is crucial to investigate the optimal extent of lymphadenectomy of laparoscopic right colectomy for right-sided colon cancer. The study protocol has been written in accordance with the Standard Protocol Items: Recommendations for Interventional Trials (SPIRIT) checklist (see Additional file 1).

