### For D2 lymphadenectomy

The D2 lymphadenectomy is performed to remove the whole anterior and posterior aspects of the mesocolon and the lymphoadipose tissues covering the anterior surface of the pancreatic head and neck, which represent the mesenteric roots of the ascending colon and the right third of the transverse colon respectively (Fig. 1). This procedure is required along the anatomical planes (embryonic planes) and is followed by ligation of the colonic supplying vessels right of the SMV and cleaning up of the surrounding lymphoadipose tissue (Fig. 2).

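### For hepatic-flexure and right-third transverse tumours, the D2 control operation is specified inconsistently at the middle colic vessels

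*Protocol article*

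**What the plan says.** All references are to the protocol article.

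- **Surgery, first paragraph**, lists what separates the arms: D2 versus D3 extent, and whether tissue is dissected over the superior mesenteric artery (SMA) and vein (SMV) and in "the tissues surrounding the root of the middle colic artery".
- **Surgery, second paragraph**, turns to what the arms share: "There is no difference between the two groups in the extent of longitudinal resection. All procedures are basically a right hemicolectomy". It then sets vessel division by tumour site and names no arm. For cecal and ascending tumours, "only the right branches of the middle colic vessels are divided centrally". For the other two sites: "Cancer of the hepatic flexure and the right third of the transverse colon requires true central ligation of the middle colic artery and vein".
- **For D2 lymphadenectomy** describes dissection along the anatomical planes, "followed by ligation of the colonic supplying vessels right of the SMV". The Fig. 2 caption repeats that level, and the Fig. 1 caption says the tissue covering the SMV stays intact. None of these makes an exception by tumour site.
- **For CME procedure** adds clearance of the SMV and SMA surface to the D2 field, followed by ligation of artery and vein at their origins.
- **Background** presents central ligation as a feature of CME and a reason to expect benefit: "In CME, the central vascular ligation (CVL) enables more radical removal of the metastatic lymph nodes".

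**The concern.** A surgeon who has a hepatic-flexure or right-third transverse tumour allocated to D2 meets two printed rules for the middle colic vessels. One, set by tumour site, calls for a true central tie. The other, set by arm, puts the ties to the right of the SMV. The article also treats central ligation as part of what makes CME different.

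If D2 surgeons follow the site rule, the arms become alike in middle colic ligation at these sites. If some follow one rule and some the other, the control operation varies by surgeon and centre across 17 hospitals. Either way, part of the contrast under test is not fixed by the plan for an eligible group of patients.

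**Working it through.** **1. Does the site rule bind both arms?** The paragraph opens with what does not differ between the groups and speaks of all procedures. No arm qualifier follows, and the arm-specific rules come later under their own headings. The Discussion likewise sets the wider transverse resection by tumour site and not by arm. Application to both arms is an inference about scope, but it is the natural reading.

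**2. The rules side by side, for hepatic-flexure and right-third transverse tumours**

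| Element | Surgery, shared paragraph | D2 section and Figs. 1–2 captions | CME section |
|---|---|---|---|
| Middle colic ligation level | True central, no arm named | Supplying vessels to the right of the SMV, no site exception | At the origins |
| Tissue over the SMV | Not addressed | Left intact | Cleared |
| Tissue around the middle colic root | Not addressed here; an arm difference in the preceding paragraph | Not addressed | Not named separately; SMA and SMV surface cleared |

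The first row is inconsistent for D2. The second row separates the arms whatever the tumour site. In the third row, the contrast is announced but never tied to a rule per arm and site.

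**3. The plan's own figure.** Inputs from Sample size calculation: 72.0% versus 80.0% 3-year disease-free survival, two-sided 5%, 80% power. With pooled variance and mean proportion 0.76:

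n = [1.960·√(2·0.76·0.24) + 0.842·√(0.72·0.28 + 0.80·0.20)]² / 0.08² = (1.184 + 0.506)² / 0.0064, which rounds up to 447 per group.

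This matches the plan; power at 447 is 80.1%.

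**4. Illustration of dilution.** The article gives neither the share f of patients at these sites nor the fraction L of benefit lost there, so both are assumed. D2 is held at 72% with 447 analysed per arm.

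Difference: Δ = 0.08·(1 − f·L).

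Power: Φ{[Δ√447 − 1.960·√(2p̄(1−p̄))] / √(0.72·0.28 + p₂(1−p₂))}, with p₂ = 0.72 + Δ and p̄ the mean of 0.72 and p₂.

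For f = 20%, L = 50%: Δ = 0.072, p₂ = 0.792, p̄ = 0.756. Then (1.522 − 1.190)/0.605 = 0.548, and power is 71%.

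| Assumed share at these sites | A quarter of benefit lost there | Half of benefit lost there |
|---|---|---|
| 20% | 7.6 points, 76% | 7.2 points, 71% |
| 30% | 7.4 points, 73% | 6.8 points, 66% |
| 40% | 7.2 points, 71% | 6.4 points, 60% |

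Complete loss is not tabulated, because the second row of the comparison in step 2 rules out identical operations.

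**The case against.** **Ligation is not dissection.** The shared paragraph concerns where vessels are tied and how much bowel is removed. It does not tell a D2 surgeon to clear the tissue around the middle colic root, and it also uses central division for cecal and ascending tumours, so the term is not reserved for CME there. This stands. A reader might infer that the control arm simply contains the experimental operation at these sites, but the article does not say so.

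**The wording may be reconcilable, and material is not shown.** The D2 phrase could describe the vessels that run to the right of the SMV and not the place of the tie. The figures and Additional file 2, to which Surgery refers for the operation, are not available and may give rules by arm and site. This stands in part. It rules out saying that the two rules can never both be met. Still, the Fig. 2 caption favours the place-of-tie reading, and the inconsistency lies between printed sentences, not in something the article left out.

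**Quality control exists.** A committee reviews CME and D2 videos, and specimen photographs show the vascular ties. This also stands in part. The only arm-specific item in the specimen grading is SMV-surface tissue in CME, and no middle colic criterion is stated.

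**Stronger consequences.** A reader might conclude that a null result could not be interpreted. That does not follow, because clearance of the SMV and SMA surface separates the arms at every site. A reader might also want a test of interaction by tumour site to reveal dilution. With half the benefit lost (8 points at the other sites, 4 at these), 447 per arm and a 40% share, the standard error of the interaction is √(0.384/178.8 + 0.3616/268.2) = 0.059. The ratio 0.04/0.059 is about 0.68, giving about 10% power; at a 20% share it is about 9%. Such a test would reveal little, and subgroup plans belong to an analysis plan that is not shown.

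**Conclusion.** The point holds as an inconsistency in the definition of the control operation, confined to hepatic-flexure and right-third transverse tumours and to the middle colic component. It rests on reading the shared paragraph of Surgery as covering both arms, and on reading the D2 section as fixing the place of the tie. Both are the natural readings, though neither is stated in so many words.

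The middle colic part of the contrast may be lost or vary by surgeon; the SMV and SMA clearance contrast remains. The effect on power cannot be determined from the article. The figures of 60% to 76% show only what the assumed shares and losses would imply. The matter deserves correction because the extent of central dissection is what the trial tests.

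**What to change.** Reconcile both paragraphs of Surgery, the D2 section with the captions to Figs. 1 and 2, and the CME section. State the middle colic ligation level and the dissection field around its root once for each arm and each tumour site. Which rule applies is the sponsor's surgical decision. If Additional file 2 already sets this out, bring the article's wording into line with it.

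Apply the reconciled definition in the existing video review and specimen review, so that middle colic handling is judged against one standard per arm and site. The photographs already have to show the tumour and the vascular ties.

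The cost is a clarification to the 17 centres and one added item in the review criteria. Sample size, randomization and endpoints are unchanged. The trial was recruiting when the article appeared, so the earlier the clarification goes out, the fewer operations are done under the ambiguous text.

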### For D2 lymphadenectomy

The D2 lymphadenectomy is performed to remove the whole anterior and posterior aspects of the mesocolon and the lymphoadipose tissues covering the anterior surface of the pancreatic head and neck, which represent the mesenteric roots of the ascending colon and the right third of the transverse colon respectively (Fig. 1). This procedure is required along the anatomical planes (embryonic planes) and is followed by ligation of the colonic supplying vessels right of the SMV and cleaning up of the surrounding lymphoadipose tissue (Fig. 2).

**Fig. 1 Fig1:**
[figure not shown]
D2 lymphadenectomy requires dissecting the supplying vessels right of the superior mesenteric vein (*SMV*) and keeping the covering lymphoadipose tissue of the SMV intact. **a** Right colic vein. **b** Pancreas neck. **c** Henle’s trunk. **d** Inferior pancreaticoduodenal vein. **e** Pancreas head. **f** Duodenum. **g** Undissected SMV

**Fig. 2 Fig2:**
[figure not shown]
During D2 lymphadenectomy, the supplying vessels are ligated right of the SMV

### For CME procedure

In addition to the dissecting area described in the D2 procedure, the CME procedure cleans up the lymphoadipose tissue on the surface of the SMA and SMV. This requires further exposure and skeletalization of the right and anterior sides of the SMV, including the surgical trunk. This exposure should remove the lymphoadipose tissues instead of the connective tissues covering the SMA, to expose its outline (Fig. 3). Then, it is followed by the ligation of the supplying vessels (both artery and vein) at their origins; the results are shown in Fig. 4.

**Fig. 3 Fig3:**
[figure not shown]
The CME procedure requires cleaning the lymphoadipose tissue on the surface of the SMA and ligating the supplying vessels at their origins. **a** Right colic artery. **b** Superior mesenteric vein. **c** Ileocecal artery and vein

**Fig. 4 Fig4:**
[figure not shown]
After complete removal of the ascending and transverse mesocolon from the roots, the pancreatic head and neck are clearly exposed during the CME procedure. **a** Pancreas neck. **b** Henle’s trunk. **c** Ligated right colic artery. **d** Pancreas head. **e** Superior mesenteric vein (surgical trunk). **f** Ligated ileocecal vessels. **g** Duodenum

### Postoperative evaluation

At the end of the surgery, the surgeon must take photos of the specimens and upload them to the central website. Both the anterior and posterior sides of the specimens are taken alongside a metric scale for calibration. The mesentery is laid out flat without external tension, indicating the sites of the tumor and vascular ties. The diameter of the tumor, the distance between the proximal and distal cutting edge to the tumor, and the distance between the most distant free mesocolon and the tumor are also precisely measured. The area of mesentery resected will be calculated after the operation by the parameters collected in the operation room.

The quality of the surgical specimens is graded from the integrity of the mesocolon by an independent review committee using a method described previously [3]. The grading of surgical specimens is classified into three groups: good (intact anterior and posterior fascia of mesocolon, intact lymphoadipose tissue from the surface of SMV in CME procedure), moderate (defects of mesocolic fascia that expose the mesocolic fat, but the incisions do not reach down to the muscularis propria), or poor (significant defects of mesocolon or disruptions extending down onto the muscularis propria). Any discrepancies of the grades will be discussed before a final grade is agreed on.

### Postoperative adjuvant therapy

The postoperative adjuvant chemotherapy is determined by the pathological results. For patients with stage III disease and patients of stage II with unfavorable histological features, 6 months of adjuvant chemotherapy using an oxaliplatin-based combination regimen is recommended. For patients of stage II without unfavorable histological features, adjuvant chemotherapy is determined by the microsatellite instability (MSI) state. For patients with microsatellite stability (MSS), single-agent chemotherapy based on 5-fluorouracil (5-FU) is recommended. For patients with MSI, we suggest just observation and regular follow-ups.

### Follow-up and data collection

The postoperative examination will be performed every 4 months in the first 2 years and every 6 months in the following 3 years. Disease-free survival (DFS) is defined as the time from randomization to the time of finding the recurrence, metastasis, or death. It is calculated on a monthly basis for the latest finding. Local recurrence is defined as a recurrence of the tumor in the surgical region, with or without elevation of serum tumor markers, and the mass of the anastomotic site must be confirmed by a pathological biopsy. A distant metastasis is defined as a metastasis that is discovered in the liver, lung, bone, or other sites by CT, MRI, or radionuclide scanning, with or without pathological examination. The postoperative complications that are included in the statistics include intra-abdominal hemorrhage, gastrointestinal bleeding, anastomotic leakage, chylous fistula, surgical site infection, including intra-abdominal infections and wound infection, intestinal obstruction, postoperative diarrhea, pulmonary infection, urinary tract infection, cardiovascular accident, cerebral vascular accident, and thrombotic disease.

### Sample size calculation

Previous retrospective studies reported that the 3-year DFS for the D2 operation ranged from 66.7% to 82.1%; the range was 77.4% to 89.1% for the CME operation [10, 15]. We estimate that the 3-year DFS for D2 and CME will be 72.0% and 80.0% respectively in this study. We expect to detect a difference of 8% in 3-year DFS between the two groups. Thus, with a significance level of 5%, a two-sided test, and 80% power, 447 patients will be required for each group. With a drop-out rate of 20%, the required sample size is 1072 patients for both arms.

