**Methods/design:**

The Radical Extent of lympadenectomy: D2 dissection versus complete mesocolic excision of LAparoscopic Right Colectomy for right-sided colon cancer (RELARC) study is a prospective, multicenter, randomized controlled trial in which 1072 eligible patients with right-sided colon cancers will be randomly assigned to the CME group or the D2 dissection group during laparoscopic right colectomy. Inclusion criteria are locally advanced colon cancers situated from the cecum to the right third of the transverse colon and clinically staged as T2-4aN0M0 or TanyN + M0. The primary endpoint of this trial is 3-year disease-free survival. Secondary endpoints include 3-year overall survival, postoperative complication rates, perioperative mortality rates, and rates of positive central lymph nodes (the station 3 nodes).

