## Methods/design

### Study design

This study is a superiority trial. The main objective is to investigate whether extended lymphadenectomy (CME) in laparoscopic colectomy could improve the oncological outcomes of patients with right-sided colon cancer, compared to laparoscopic colectomy with D2 lymphadenectomy.

The study design is a prospective, multicenter, randomized, two-arm, parallel-group, single-blind clinical trial. The enrolled participants with right-sided colon cancers, including cancers situated from the cecum to the right third of the transverse colon, will be divided into two groups: the laparoscopic CME group (the intervention group) and the laparoscopic colectomy with D2 dissection group (the control group).

According to the final pathological results of surgical specimens, patients with stage III colon cancer or stage II disease with unfavorable histological features will be required to undergo adjuvant chemotherapy for 6 months. The oxaliplatin-based combination regimen will be recommended.

All the patients will be followed up regularly for at least 5 years, according to the follow-up protocol recommended by the NCCN guidelines. All patients are required to undergo postoperative examinations every 4 months for the first 2 years and every 6 months thereafter until 5 years after the surgery. Signs of suspected disease relapse including local recurrence (LR) or distant metastasis (DM) will be closely observed and monitored. The schedule of this trial is shown in Table 1.

**Table 1 Tab1:** Schedule of enrollment, intervention, and assessments for the RELARC trial

	Study period										
	Enrollment	Allocation	Post-allocation								Close-out
Timepoint	–2 weeks	0	Surgery	4 months	8 months	1 year	16 months	20 months	2 years	30 months	3 years
Enrollment:											
Eligibility screen	X										
Informed consent	X										
Allocation		X									
Interventions:											
Laparoscopic D2 operation			X								
Laparoscopic CME operation			X								
Assessments:											
Disease-free survival				X	X	X	X	X	X	X	X
Overall survival				X	X	X	X	X	X	X	X
Postoperative complication			X								
Perioperative mortality			X								
Central lymph node assessment			X								

Our study is expected to last 7 years, including 4 years for recruiting patients and 3 years for follow-up.

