### Randomization and blinding

Patients enrolled in this study will be randomly assigned into either the study group or the control group. The random numbers are generated using Statistical Analysis System (SAS) software to ensure that patients are randomly divided into two groups with an allocation ratio of 1:1. A central randomization system will be employed, and all the researchers must register at the website of the research system. When a researcher has chosen a certain patient, he/she should log on to the webpage and upload the basic information on the patient before acquiring the random grouping schemes.

All the patients are blinded to the surgical approach that they are going to receive, and will be required to sign the informed consent before being enrolled in the study. Obviously, it is impossible to blind the surgeons who will perform the surgeries. However, all the surgeon researchers will be required to limit potential co-interventions as much as possible. In addition, the result assessment will be made by independent researchers who are blinded to the surgical procedures.

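### The 20% drop-out allowance is applied as a 1.2 multiplier, so 1072 patients fall short of the 894 evaluable patients that the protocol requires

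*Protocol article*

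**What the plan says.** The Sample size calculation section of the protocol article sets the planning rates: "We estimate that the 3-year DFS for D2 and CME will be 72.0% and 80.0% respectively in this study". It then derives the number before any allowance for loss: "Thus, with a significance level of 5%, a two-sided test, and 80% power, 447 patients will be required for each group". The last step adds the allowance: "With a drop-out rate of 20%, the required sample size is 1072 patients for both arms". Allocation is 1:1 (Randomization and blinding), so 1072 means 536 per arm. The Abstract repeats the total as "1072 eligible patients with right-sided colon cancers". The article prints no inflation formula and does not say whether the 20% is a share of the patients randomised or an addition to the evaluable number.

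**The concern.** A drop-out rate ordinarily means the share of enrolled patients who are lost. The evaluable number is then divided by one minus that rate. Multiplying by one plus the rate gives too small a total, because the loss applies to the larger, inflated number. The stated total looks like the result of that multiplication.

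Sample size, drop-out rate and power are stated together, and readers will use them together. The DSMB is to review drop-outs (Data and safety monitoring), and the exit criteria under Study subjects can remove patients after enrolment. Anyone monitoring losses against the stated 20% would believe that 80% power is safe up to that level. If the inflation is wrong, the margin ends earlier.

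**Working it through.** **Inputs**, all from the Sample size calculation section except the allocation ratio: 3-year DFS 72% (D2) and 80% (CME), difference 0.08; two-sided 5%; 80% power; 447 per group; drop-out 20%; total 1072; 1:1 allocation (Randomization and blinding).

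**1. Reproduce 447 per group.** Two-proportion formula with pooled variance under the null, no continuity correction, mean rate 0.76:

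n = [1.960 × √(2 × 0.76 × 0.24) + 0.842 × √(0.72 × 0.28 + 0.80 × 0.20)]² / 0.08²

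= (1.1838 + 0.5061)² / 0.0064 = 446.2, rounded up to 447.

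The stated figure reproduces exactly. It is therefore the number before drop-out, and 2 × 447 = 894 is the evaluable total required.

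**2. Reproduce 1072.**
- Multiplying: 894 × 1.20 = 1072.8 (447 × 1.2 = 536.4 per arm). Rounded down, this gives 1072 (536 per arm).
- Dividing: 894/0.80 = 1117.5. Rounded up, this gives 1118 (559 per arm).

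The stated total matches the multiplication. That the protocol multiplied is an inference from the arithmetic; the shortfall in step 3 does not depend on it.

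**3. Apply 20% drop-out to 1072.** 1072 × 0.80 = 857.6, or 428.8 per arm. The shortfall against 894 is 36.4 evaluable patients. In randomised patients it is 1118 − 1072 = 46, which is 46/1072 = 4.3%.

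**4. Power on the same method.** Power = Φ{[0.08 × √n − 1.1838] / √0.3616}, where 0.3616 = 0.72 × 0.28 + 0.80 × 0.20.

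| Evaluable per arm | How reached | Power |
|---|---|---|
| 447 | the stated requirement | 80.1% |
| 428.8 | 1072 randomised, 20% lost | 78.4% |
| 447.2 | 1118 randomised, 20% lost | 80.1% |

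**5. Drop-out rate that 1072 covers.** 1 − 894/1072 = 0.166, so 16.6%.

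**The case against.** The strongest reply concerns the power consequence. The 78.4% assumes that every patient who drops out contributes nothing. DFS is defined as a time from randomization, and the Statistical analysis section plans Kaplan-Meier and log-rank methods, in which a patient counts until censoring. With exponential DFS through 72% and 80% at 3 years (hazard ratio 0.679) and 1072 randomised, the Schoenfeld formula gives:

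- 20% lost at time zero, 3-year events only: about 206 events, power 79.2%.
- 20% lost gradually by year 3 (assumed exponential), 3-year events only: about 232 events, power about 83.7%.
- The same drop-out hazard, with all follow-up over 4 years of uniform recruitment plus 3 years counted: about 328 events, power about 94%.

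This stands as a limit on the consequence. Under the planned test, 1072 is at worst within one point of 80%, and losses through the exit criteria are likely to be early, nearer the first case. It does not repair the statement. The section sizes the trial on 3-year proportions and adds its own allowance for loss, so its figures must agree on that basis.

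A second reply is that the 20% could be an addition to the evaluable number, and that the full protocol might say so. Nothing in the article defines it that way, and the usual meaning of a drop-out rate is the other one. Even on that reading, 1072.8 should round up to at least 1073.

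A third is that the planning rates were chosen from wide retrospective ranges (66.7% to 82.1% for D2, 77.4% to 89.1% for CME), an uncertainty far larger than 1.6 points of power. That is true and bears on the importance of the error, but not on whether the sentence is right.

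**Conclusion.** The concern holds. With the 20% read as the share of randomised patients lost, the stated 447 per group, 20% drop-out and total of 1072 are incompatible: 1072 leaves 857.6 evaluable patients where 894 are required. The total that satisfies both 20% and 80% is 1118.

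The practical size is minor. On the protocol's two-proportion method, with no information from patients who drop out, power is 78.4% against the 80% planned, a loss of about 1.6 points. Under the planned log-rank test the loss is smaller or absent. The trial is not seriously underpowered, and no endpoint, test or significance level changes. It is a definite arithmetic error in the primary sample-size statement, and the Abstract carries the same total.

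**What to change.** Reword the final sentence of the Sample size calculation section. No further enrolment is needed. Either of these statements is correct with 1072 kept:

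- With 1072 patients randomised and 20% drop-out, about 429 per arm remain evaluable, and power is about 78% if patients who drop out contribute no data.
- With 1072 patients randomised, 80% power is kept for drop-out of up to 16.6%.

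If the sponsor prefers to keep both 20% drop-out and 80% power, the total becomes 1118 (559 per arm), here and in the Abstract. In every case, say that the drop-out rate is a proportion of the patients randomised.

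The first two options cost one sentence and a slightly less favourable stated power or drop-out allowance. The third costs 46 more patients.
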